### Allocating patients to study therapists

The assignment of a patient to a study therapist is done by the main study coordinator. Besides the randomisation result, time availability (for the weekly sessions), other preferences (eg, gender of the therapist, treatment location) of both the patient and the therapist, and the therapist’s current study case load will be taken into account. Due to feasibility reasons, we refrained from considering further factors (eg, balancing patients with or without personality disorders at the therapist level). In rare cases, a randomised patient may not be allocated to a study therapist. This occurs when all therapy slots in the respective study group are filled, or when no available therapist can agree with the patient on a suitable time for their weekly appointments. After allocation, the main study coordinator informs the local study coordinator, and the respective therapist will receive the patient files and all relevant information and documents for the process assessments. The therapist is instructed that they should offer an appointment as soon as possible and start treatment.

### Patient treatments

Basic conditions of treatments will be equal between MAFT-D and TAU. Patients will receive weekly 50 min sessions (regular frequency and length). Postassessment will take place at week 20, first follow-up at week 35, second and third follow-up after 20 and 36 months. Treatments can be short-term or long-term depending on the patient’s and therapist’s agreement and the sessions granted by payers. According to usual care, all treatments must begin with probatory sessions (2–4 sessions before official start of therapy). Following this, the number of sessions requested by therapists and patients, and covered by payers in Germany, varies, ranging from at least 12 to up to 80 therapy sessions for CBT and up to 100 for PDT. All sessions will be video recorded. Therapists will treat two study patients on average. The costs of treatments are fully covered by statutory health insurances in Germany.

### Psychotherapy training

TAU-D and MAFT-D therapists will continue to participate in their regular training courses. Group supervisions of treatments will be carried out by experienced supervisors either with MAFT-D specific focus or according to the usual procedure. Supervision frequency and format (one session for every four therapy sessions, in person, additional individual supervision is permitted in accordance with the regulations of the specific institute in the event of crises or for questions regarding the report for the health insurance company) represents the common standard and legal requirement for trainee therapists in our country. This frequency might deviate from other clinical trials or the clinical practice in other regions. The supervision frequency may influence outcomes but also reflects local real-world practice conditions, adding ecological validity to the study. The supervision groups are fixed, and in order to participate, the therapist must have already started at least one study therapy. Group supervisions will occur monthly or biweekly, with patients being discussed for varying amounts of time (10–50 min per case). Supervisors will receive regular supervision fees. The hours of the workshop for the MAFT-D group will replace other non-mandatory courses of the regular training.

### Experimental intervention

Therapists randomised to MAFT-D will receive a 2-day workshop (approx. 15 teaching units, 11.5 hours) followed by group supervision carried out by supervisors who will also be trained in MAFT-D. The initial workshops will take place in person (for therapists and supervisors separately). Central elements are a theoretical introduction (150–180 min) and role plays based on individual case examples (approx. 45 min per participant). The number of lecturers depends on the overall group size (one lecturer and max. eight therapists per role play subgroup). In the case of unexpected absences (eg, illness) and for therapists who are unable to attend at the originally planned workshop dates, catch-up workshops will be offered. Catch-up workshops consist of smaller groups and are shorter (approx. 10 teaching units, 7.5 hours) but are more intense due to more frequent participation in role plays.

AFT is a transtheoretical training concept initially developed by Eubanks-Carter *et al*^36^ focusing on alliance ruptures and aiming at enhancing therapists’ interpersonal skills to (a) sensitively recognise alliance ruptures, (b) tolerate negative affects and (c) meta-communicate using video-recorded sessions, role plays and mindfulness exercises.^13 36 40 41^ We have translated the AFT into German and tested and modified it in pilot studies.^37 40 41^ Our modifications concern^31 71 72^: (a) strong standardisation of the supervision process, (b) verbalisation of the affective experience exclusively via ‘doubling’ (psychodrama technique) immediately after the role plays, (c) structured focussing on therapist‘s own contribution (vulnerabilities, biographical relationship experiences; based on pre work^72 73^) and (d) active role of supervisors in practising meta-communication (‘prompting’). The modifications were made because, in our experience, there is a tendency in supervision groups to rationalise, intellectualise and cognitively exchange concepts and strategies, which can also conceal difficulties in opening up affectively (resistance to the perception of subjective or objective countertransference^73 74^) or ‘hiding’ of alexithymic tendencies (ie, difficulties in perceiving and expressing emotions^75^). The modifications aim to enhance the focus on the perception and verbalisation of emotions, minimise intellectualising after role plays, and foster a more non-judgemental atmosphere within the supervision group. Supervision follows the following standardised procedure (duration approx. 45 min per patient): (A) Mindfulness exercise (to increase awareness and openness to one’s own emotional experience), 3–4 min; (B) Introduction of the patient and characteristics of the therapeutic relationship with this patient (B1: verbally, B2: video sequence from last therapy session, B3: ‘screenplay’ of an alliance rupture), 8–10 min; (C) First role-play and ‘doubling’ (C1: Supervisee in therapist role, supervision group member in patient role, C2: ‘Doubling’, psychodrama technique, to deepen the affective insight and enable access to blind spots), 7–9 min; (D) Second role-play and ‘doubling’ (D1: Supervisee in patient role, further supervision group member in therapist role, D2: ‘Doubling’, D3: Supervisor asks group members who were in the patient role how they felt), 10–13 min; (E) Third role-play and own contributions (E1: Supervisee in therapist role, tries out new behaviour, practises meta-communication, uses suggestions from the supervisor—prompting, E2: Supervisor asks what the rupture may have to do with supervisee’s vulnerabilities, whether own biographical issues may have been ‘triggered’, which feelings may be difficult to bear due to personal experiences), 6–8 min.

Supervisors belonging to MAFT-D will receive a 2-day workshop before the start of study therapies (same contents as for therapists but separately), followed by a monthly 2-hour online training to refine MAFT-D-specific supervision skills and discuss questions.

To ensure consistency across centres, MAFT-D therapists of different centres will be trained together. The same applies to supervisors. There will be a fixed group of lecturers (experienced psychotherapists and experienced in conducting MAFT-D-specific workshops and supervision).

### Sample size calculation, number of study participants

Depressive symptoms: There are no prior studies that closely align with our study in terms of study population, intervention and measurement instruments. In our view, the chosen reference Bambling *et al*^45^) represents the best available compromise, as it examines a population of depressed patients, employs an alliance-focused supervision approach and uses the BDI-II as a measurement instrument. Accordingly, we assume a higher reduction in BDIII after 20 weeks in MAFT-D compared with TAU of 4.0 BDI-II units with a SD of 7.3 BDI-II units. To detect such an effect with a type I error of .05 (two-sided hypothesis), a power of .90, an intracluster correlation coefficient of 0.05, and a cluster size of 2 patients per therapist on average, we need 76 therapists and 152 patients in total (38 therapists and 76 patients per group, PASS 15, tests for two means in a cluster-randomised design).

Treatment dropout: We expect that MAFT-D will reduce the treatment dropout rate after 20 weeks from 30% to 12.5%, corresponding to an OR of 3.0. The expected dropout rate of 30% for TAU is a conservative estimate based on a recent meta-analysis (35% dropout)^7^ and numbers in our own clinic (n=3.357 depressed patients; 33% dropout). Previous studies on different AFT approaches reported a difference in treatment dropout rates of 17.5% or greater (Bambling *et al*: IG1=6.1%, IG2=3%, CG=35%; Constantino *et al*: IG=0%, CG=27.3%; Muran *et al*: IG=20%, CG1=37%, CG2=46%).^45 46 76^ With identical design effects, 58 therapists and 116 patients per group (116 therapists, 232 patients in total) are needed to detect this difference (PASS 15, test for two proportions in a cluster-randomised design). We expect that 3% of the randomised sample are not part of the full analysis set (oriented on numbers from the trial of Schramm *et al*^77^) due to the lack of any data postrandomisation.^78^ Thus, based on the larger sample size required for dropout, a sample of 120 therapists and 240 patients in total has to be enrolled.

Based on previous psychotherapy trials,^77 79^ we expect a loss to follow-up of 15% (of therapists with their patients) at postassessment in BDI-II measurement. With the planned number of sample size and the assumed loss to follow-up, we can prove the assumed effect. We assume a non-compliance rate for the (per protocol, PP) BDI-II analysis (eg, failure to complete 12 sessions within 20 weeks, change in antidepressant medication, use of additional treatments) of 35%.

We expect that 20% of patients and therapists decline study participation, and 15% of therapists and 50% of patients do not meet inclusion criteria. Consequently, 178 therapists and 600 patients need to be initially invited in order to assess eligibility in 142 therapists and 480 patients, in order for 120 therapists and 240 patients to participate in the study and finally analyse 116 therapists and 232 patients. To ensure that the target sample size is achieved, up to five additional units may be recruited as a buffer (ie, 40 therapists, 80 patients, 10 supervisors). This precaution is necessary due to the interdependent nature of the units, where unexpected short-notice dropouts could compromise the participation of entire units.

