### Recruitment

Recruitment will take place at the cooperating study centres (see above). Additional centres will be involved in the event of recruitment difficulties. Recruitment started in July 2024 and is ongoing.

The standard group size for group supervision is four participants, which applies to the study and also to routine therapy training. Consequently, units of eight therapists must usually be recruited per institute. Some institutes allow smaller group sizes. However, a group consisting of only two participants on a long-term basis (more than 4 months) is considered a protocol violation. Combining study therapists from different training institutes at one location in a supervision group is permitted. The groups can also be filled with non-study participants. Changing the format from group to individual supervision is generally not permitted within the context of the study. Recruitment methods for therapists include project promotion through email, advertisement in lectures/seminars. Patients are recruited from the regular outpatient pool. Recruitment period is 21 months for patients and 16 months for therapists. A key challenge in this study is the time-sensitive recruitment of integrated units comprising patients, therapists and supervisors. Due to the interdependence of these participants, unexpected, short-notice dropouts may jeopardise not only the involvement of the individual concerned but also the participation of the entire unit. To ensure the required sample size is reached, we plan to recruit up to 5 additional units (ie, 40 therapists, 80 patients and 10 supervisors) as a buffer for potential dropouts. Patients, therapists and supervisors will receive incentives for study-related expenses (assessments, video recordings and travel).

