### Statistical analyses

Results are reported according to the Consolidated Standards of Reporting Trials (CONSORT) statement.^124^ Analyses are carried out with standard software: SPSS, V.29 or newer (IBM), SAS, V.9.4 or newer (SAS Institute), or R (V.4.3.3). A statistical analysis plan that contains the details of all planned analyses will be finalised before database lock.

Descriptive data are presented overall and separated by randomised group. As descriptive statistics, mean, SD, median, first and third quartile or minimum and maximum are calculated for continuous variables. For categorical variables, absolute and relative frequencies are reported.

First primary outcome (hypothesis I): We use a linear mixed model with repeated measures with changes from baseline as dependent variable, IG, therapeutic approach (CBT vs PDT), time and comorbid SCID5 personality disorder (yes vs no) as fixed effects, baseline BDI-II score as covariate, time by IG interaction, and cooperation centre, supervision group (if possible), therapist (=cluster) and patient as nested random effects. The interaction term is eliminated from the model if the corresponding interaction p value is >0.15. Measurement points up to and including the first follow-up (within the current funding period) will be considered. The contrast of the IG after 20 weeks is the result of the primary analysis. This result is considered in a confirmatory manner according to the approach described below. If the model fails to converge due to the complex cluster structure and variance components are estimated as zero, we will simplify the model stepwise by removing random effects.

Second primary outcome (hypothesis II): We perform a mixed logistic regression with the binary variable patient dropout after 20 weeks (yes vs no) as dependent variable, IG, therapeutic approach (CBT vs PDT) and comorbid SCID-5 personality disorder (yes vs no) as fixed effects, and cooperation centre, supervision group (if possible), and therapist as nested random effects.

The two primary hypotheses are hierarchically ordered and tested one after the other at the two-sided 5% level. Hypothesis II is only tested if hypothesis I could be rejected. If hypothesis I cannot be rejected, hypothesis II is no longer examined confirmatory but exploratory. This procedure ensures a family-wise type I error of 5%.

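### The dropout sample size allows for clustering by therapist but not by supervision group, so at 116 patients per arm the 90% power is an upper bound

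*Protocol article*

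**What the plan says.** The protocol article, in its section on sample size calculation and number of study participants, plans the BDI-II comparison with "a type I error of .05 (two-sided hypothesis), a power of .90" and "an intracluster correlation coefficient of 0.05, and a cluster size of 2 patients per therapist on average". For dropout it expects MAFT-D to "reduce the treatment dropout rate after 20 weeks from 30% to 12.5%, corresponding to an OR of 3.0", and then states: "With identical design effects, 58 therapists and 116 patients per group (116 therapists, 232 patients in total) are needed to detect this difference". Power is not restated for dropout. After a 3% allowance for patients outside the full analysis set, enrolment follows from dropout: "based on the larger sample size required for dropout, a sample of 120 therapists and 240 patients in total has to be enrolled".

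Other sections describe a further level of clustering:

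- Recruitment: "The standard group size for group supervision is four participants".
- Patient treatments: therapists treat two study patients on average.
- Psychotherapy training: supervision groups are fixed.
- Inclusion criteria for therapists and supervisors: supervisors agree not to supervise study therapists of the other condition.
- Statistical analyses: supervision group is listed, where possible, as a nested random effect for both primary outcomes.

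**The concern.** After a two-day workshop, MAFT-D reaches therapists through group supervision. Patients of different therapists in one group therefore share a supervisor and a group, all within one arm. Any variation between supervisors or groups in their effect on dropout makes those patients' outcomes correlated, and that inflates the variance of the arm comparison. The analysis model allows for this source of variance, whereas the sample-size calculation treats it as zero.

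Dropout is the endpoint that fixes enrolment, so an optimistic design effect there has no larger requirement elsewhere to absorb it. At stake is how a reader judges the trial's ability to detect the planned dropout difference.

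**Working it through.** **Inputs from the protocol.** Two-sided 5% level, power 0.90, dropout 30% against 12.5%, therapist ICC 0.05, two patients per therapist, 116 patients per arm analysed. For BDI-II: difference 4.0, SD 7.3, 15% loss to follow-up.

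**Reproducing the plan's figures.** With unpooled variance, the number per arm without clustering is (1.960 + 1.2816)² × (0.30 × 0.70 + 0.125 × 0.875) / 0.175² = 10.507 × 0.3194 / 0.0306 = 109.6. The design effect is 1 + (2 − 1) × 0.05 = 1.05, and 109.6 × 1.05 = 115.1, which rounds up to 58 therapists and 116 patients. Power at 116 is 0.902. (Pooled variance gives 0.894.) Enrolment: 232 / 0.97 = 239.2, hence 240. The plan's figures follow from its inputs, with a reserve of about one patient per arm.

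**Patients per supervision group.** Four therapists × two patients = 8. The buffer units give the same ratio: 80 patients / 10 supervisors = 8. With 60 therapists per arm there are about 60 / 4 = 15 groups per arm.

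**Adding the missing level.** Let ρ be the correlation between patients of different therapists in one supervision group, and m the number of study patients per group. The design effect becomes 1 + (2 − 1) × 0.05 + (m − 2) × ρ. The documents give no value for ρ, so the range below is an assumption. The planned 0.05 is read as the total correlation between two patients of one therapist. On that reading ρ cannot exceed 0.05, and at 0.05 no therapist-specific variance is left.

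Power is Φ(0.175 / √(0.3194 × DE / 116) − 1.960). For m = 8 and ρ = 0.02, DE = 1.17, the ratio is 3.083, and power is Φ(1.123) = 0.869.

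| ρ | DE, m = 8 | Power, m = 8 | Power, m = 6 | Power, m = 4 |
|---|---|---|---|---|
| 0 | 1.05 | 0.902 | 0.902 | 0.902 |
| 0.01 | 1.11 | 0.886 | 0.891 | 0.897 |
| 0.02 | 1.17 | 0.869 | 0.880 | 0.891 |
| 0.03 | 1.23 | 0.853 | 0.869 | 0.886 |
| 0.05 | 1.35 | 0.819 | 0.847 | 0.875 |

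Pooled variance lowers the m = 8 column by about one point (0.877, 0.859, 0.842 and 0.806 for ρ of 0.01 to 0.05).

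**BDI-II.** After 15% loss, 120 × 0.85 = 102 per arm. Power is 0.968 at ρ = 0 and 0.960, 0.951, 0.942 and 0.920 at ρ = 0.01, 0.02, 0.03 and 0.05 with m = 8. It stays above 0.90 throughout.

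**The buffer.** If all 80 extra patients were recruited, (240 + 80) × 0.97 / 2 gives about 155 per arm. Dropout power with m = 8 and ρ = 0.05 would then be 0.913.

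**The case against.** The arithmetic is not wrong: 116 per arm follows from the stated inputs, and the text openly says which clustering was counted. A reader might infer that the sample size was miscalculated. The documents do not support that; what is open to question is a design assumption, not a computation.

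The size of the loss rests on a correlation that the documents do not give. At 0.01 it is under two points, and the largest loss needs the boundary value of 0.05. Eight patients per group is the standard case, not a constant: the Recruitment section allows smaller groups and places filled by non-study participants, and the Figure 1 legend allows one or three patients per therapist. The optional buffer could restore power above 0.90 even at 0.05. These points stand, and they are why the result is given as a range. They do not remove the concern. The buffer is optional and is meant for short-notice losses of units, and any positive ρ still takes power at the planned size below the value used.

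A reader might also infer that the testing hierarchy makes the power statement wrong, because "Hypothesis II is only tested if hypothesis I could be rejected". It does not. The plan claims no joint power, planning each hypothesis at its own power is common in fixed-sequence testing, and the gate is disclosed. On the plan's own assumptions, and treating the tests as independent, confirmatory power for dropout is 0.968 × 0.902 = about 0.87 with no group correlation, a cost of about three points. Larger costs appear only if a smaller BDI-II effect is assumed than the plan states.

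**Conclusion.** The point holds in a limited form. The calculation that sets enrolment omits a level of clustering that the protocol describes and both primary models include, and it has almost no slack. At 116 per arm, 0.90 is therefore an upper bound for dropout. With eight patients per group, power is about 0.89 to 0.82 for an assumed group correlation of 0.01 to 0.05. With four to six it is about 0.89 to 0.90 at 0.01 and 0.85 to 0.88 at 0.05. The first primary endpoint is not threatened.

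A reader might take 0.82 as the power that the design delivers. The documents do not support that: it is the edge of an assumed range. The planned dropout model already lists supervision group where possible, so the point concerns the stated power, not the planned estimate or test. Severity is minor to moderate.

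**What to change.** Keep the enrolment. In the sample-size section:

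- Restate the design effect as 1 + (2 − 1) × ICC(therapist) + (m − 2) × ICC(supervision group), with m the number of study patients per group.
- Report dropout power over a stated range of ICC and m in place of the single 0.90.
- Say how far the optional buffer of 80 patients would offset the loss.
- Optionally, add that confirmatory power for dropout after the gate is about 0.87 with no group correlation. This is extra information, not a correction.

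The cost is a few sentences and a small table. The stated power for dropout becomes less favourable; recruitment, endpoints and analysis model do not change.

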### Endpoints, variables and instruments

Primary endpoints: Change in patient-rated depressive symptoms will be measured using the total score of (BDI-II, change=difference from baseline to 20 weeks after baseline),^66 80^ which is one of the most commonly used self-rating scales to assess depressive symptoms and is particularly recommended for monitoring the severity of depressive symptoms over time in clinical populations.^1^ Items are rated from 0 ‘not present’ to 3 ‘severe’. The total score is the sum of all 21 items (0–63). Good psychometric properties (reliability, validity, sensitivity to change) were demonstrated for the German version.^66^

Premature therapy dropout is a dichotomous variable determined by patient interview. It is defined as the patient’s decision to end therapy contrary to the initial agreement with the therapist, excluding premature terminations unrelated to therapy quality, such as those due to serious illness of the patient or therapist or moving to a different city. In case patients cannot be reached, interviews will be conducted with the therapist, and the patient is classified as a dropout.

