BA, baseline assessment; BDI-II, Beck Depression Inventory–II^66 80^; BFI-10, Big Five Inventory–10^112^; BIFS, Beth Israel Fidelity Scale^58^; CAMSQ, Certainty about Mental States Questionnaire^115^; CCSS-S, Clinical Communication Skills Scale–short^107^; CSQ-8, Client Satisfaction Questionnaire-8, modified to supervision satisfaction^94^; CSSRI, Client Sociodemographic and Service Receipt Inventory^59^; CSSR-S, Colombia Suicide Severity Rating Scale^69^; ERQ, Emotion Regulation Questionnaire^97^; Empathy Scale^105^; FDEB, Fragebogen dysfunktionaler elterlicher Beziehungsstile^110^; FIS, Facilitative Interpersonal Skills^90^; FUP, follow up assessment; GAD-7, Generalised Anxiety Disorder Scale-7^83^; GRID-HAM-D, GRID Hamilton Rating Scale for Depression^81 82^; IIP-32, Inventory of Interpersonal Problems-32^87^; IMI-R, Impact Message Inventory^126^; INEP, Inventory for the assessment of Negative Effects of Psychotherapy^125^; ISC-G, Interpersonal Sensitivities Circumplex–German^114^; MOCPI, Mediators of Change in Psychotherapy Inventory^109^; OPD, operationalised psychodynamic diagnosis; OPD-SQS, OPD-Structure Questionnaire, short version^86^; PATHEV, Patientenfragebogen zur Therapieerwartung und Therapieevaluation^118^; PHQ-15, Patient Health Questionnaire-15^84^; PIL, Psychodynamic Interventions List^104^; Post, post-assessment; PSQ-Mod, Post-Session-Questionnaire, modified version^102 103^; Relational Manner–state and trait, and the Skills Change Index are both part of the Trainee Current Practice Report originally used in the SPRISTAD trial and currently under psychometric evaluation^127^; PSQ-Mod, Post-Session-Questionnaire, modified version^102 103^; 3RS, Rupture Resolution Rating System^123^; SANB, Skala Angst vor negativer Bewertung^128^; SCID-CV/PD, Structured Clinical Interview for DSM-5 Disorders, Clinician Version/ Personality Disorders^60 61^; TAS-20, Toronto Alexithymia Scale 20; VAS, Visual analogue scale^129^; WAI-SR, Working Alliance Inventory, short revised^100^; WHOQOL-BREF, WHO Quality of Life, short version^89^.

The number of items in the report on important events depends on which event (eg, study dropout, therapy dropout, hospitalisation) occurred. Important events should be reported as soon as possible, and the reporting is independent from scheduled sessions.

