These analyses will be conducted either in the full analysis set, which is as complete as possible and as close as possible to the intention-to-treat ideal of including all randomised participants,^118^ or in the sample excluding randomised participants who did not receive a single dose (ie, one therapy session). Missing values are implicitly imputed by the chosen model. This allows for a (modified) intention-to-treat analysis, which results in unbiased estimations under the missing-at-random assumption. Missing values for treatment dropout can only be due to both patient and therapist leaving the study.

Sensitivity analysis for primary endpoints: To investigate the robustness of the results of the primary analyses, we will conduct sensitivity analyses with multiple imputation by chained equations as the imputation strategy. Additionally, primary analyses are repeated in the PP sample. Definition PP sample: patients who receive therapy by trained or non-trained and accordingly supervised therapists as intended by their group allocation without protocol deviations. Protocol violations include: (a) patient’s use of non-allowed medications (eg, newly prescribed antidepressant) or not allowed concurrent psychological treatments, (b) less than 12 completed therapy sessions at the end of week 20 (not relevant with respect to the outcome therapy dropout), (c) participants belonging to the IG, but not receiving the intervention in the intended dose, (d) non-compliant completion of assessments (eg, too early or too late). It will be documented (a) whether the protocol violation occurred during or after the study therapy or overlapping and (b) the measurement time point(s) for which the protocol violation is relevant.

Secondary outcomes: Secondary outcomes are examined exploratorily with analogous methods appropriate for the scale level (ie, mixed linear, logistic, ordinal, or Poisson/negative binomial regression). The contrast of the IG versus CG at week 35 of BDI-II changes from baseline of the model of the first primary outcome is used as a result of secondary outcome analysis. Analyses will be conducted up to and including the first follow-up (week 35) and will be repeated at a later time to include the subsequent measurement points (ie, follow-ups 2 and 3).

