### Ethics and dissemination

The study is being conducted in compliance with the protocol, Good Clinical Practice, the Declaration of Helsinki and the CONSORT statement.^125^ All study patients, therapists and supervisors need to provide written informed consent to the main study team prior to their inclusion (see onlinesupplemental materials 1^4^: Example of Patient Consent Form; Example of Therapist Consent Form a/b; Example of Supervisor Consent Form). Study participation is completely voluntary and can be cancelled at any time without negative consequences. Patients who terminate study participation can continue their treatment. The study was approved by the Ethics Committee of the Psychologische Hochschule Berlin (EK2024/11). Additionally, we obtained secondary votes in each federal state where one or more study centres are located. Any major modifications to the study protocol will be covered by amendments and communicated to the relevant parties (eg, Data Safety and Monitoring Board, DSMB, see below). All personal data collected as part of the study, following the consent of the study participant, are subject to confidentiality and the provisions of the General Data Protection Regulation. All questionnaire, interview and rating data are collected pseudonymously within the secuTrial eCRF and REDCap surveys. This means that the participant’s name and all direct identifiers are replaced with a pseudonym, making reidentification outside of the study no longer possible. Access to the code key list that enables the association between study data and personal information of the study participant is limited to study staff explicitly authorised by the PI. The code key list is stored securely and separately from all other study data (eg, questionnaire data). The individual code key will be permanently erased following the completion of data collection and after the obligatory archiving time frame.

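### The fallback for unreachable patients codes them all as therapy dropouts, including endings that the endpoint's own definition excludes

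*Protocol article*

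**What the plan says.** In the protocol article, under *Endpoints, variables and instruments*, the second primary endpoint is set out in three steps.

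- Source: "Premature therapy dropout is a dichotomous variable determined by patient interview".
- Definition: "It is defined as the patient’s decision to end therapy contrary to the initial agreement with the therapist", and then "excluding premature terminations unrelated to therapy quality, such as those due to serious illness of the patient or therapist or moving to a different city".
- Fallback: "In case patients cannot be reached, interviews will be conducted with the therapist, and the patient is classified as a dropout".

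Under *Statistical analyses*, on missing data: "Missing values for treatment dropout can only be due to both patient and therapist leaving the study".

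Three other places bear on the point. In the notes to the table under *Measurement time points*, the length of the therapist's event report "depends on which event (eg, study dropout, therapy dropout, hospitalisation) occurred", so leaving the study and leaving therapy are kept apart. *Ethics and dissemination* says: "Patients who terminate study participation can continue their treatment". The same table gives the dropout interview flexible timing and does not tie it to the week-20 assessment.

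**The concern.** The fallback sentence places no condition on what the therapist reports. The therapist is asked, but as written the answer cannot change the code. This conflicts with the definition immediately before it. Someone who has moved away or is seriously ill may well be hard to contact. The definition leaves that person out of the event count and the fallback puts the person in.

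If the rule is followed literally, failure of the study team to make contact is mixed into an endpoint meant to describe a decision about treatment. With equal miscoding in the arms, the added events pull the odds ratio towards 1 and use up power on the endpoint that fixes the sample size. With unequal miscoding, the comparison is biased in a direction nobody can predict. This is a stated rule for a primary endpoint, not a detail left to the statistical analysis plan.

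**Working it through.** **The passages side by side**

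| Situation of an unreachable patient | Definition | Fallback as written |
|---|---|---|
| Patient chose to stop against the agreement | dropout | dropout |
| Therapy ended through illness or relocation | not a dropout | dropout |
| Therapy still running (only if the interview is attempted at that stage) | not a dropout | dropout |

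The second row is a direct contradiction. The third depends on when the interview is held, which the article leaves open.

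**Inputs for scale** (*Sample size calculation*): dropout 30% under TAU and 12.5% under MAFT-D, two-sided 5% level, 90% power, intracluster correlation 0.05, on average 2 patients per therapist, 116 patients per group.

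**The plan's own figure first.** The design effect is 1 + (2 − 1) × 0.05 = 1.05. With unpooled variance,

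n = [0.30 × 0.70 + 0.125 × 0.875] × (1.960 + 1.282)² / (0.175)² = 109.6 per group.

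Multiplied by 1.05 this is 115.1, so 58 therapists and 116 patients per group, 232 in total, as stated. The effective size per group is 116 / 1.05 = 110.5, the standard error is √(0.319375 / 110.5) = 0.0538, and power is Φ(0.175 / 0.0538 − 1.96) = 0.902. The sample size reproduces and is not in dispute.

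**Effect of miscoding.** Let u be the share of true non-dropouts coded as dropouts. The observed rate is p + u(1 − p). The documents give no value for u, so 2% and 5% are assumptions, applied first equally to both arms.

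| u | TAU | MAFT-D | Odds ratio | Power at 116 per group |
|---|---|---|---|---|
| 0 | 30.0% | 12.5% | 3.00 | 0.90 |
| 2% | 0.30 + 0.02 × 0.70 = 31.4% | 0.125 + 0.02 × 0.875 = 14.25% | 2.75 | 0.87 |
| 5% | 0.30 + 0.05 × 0.70 = 33.5% | 0.125 + 0.05 × 0.875 = 16.9% | 2.48 | 0.83 |

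In patients: true non-dropouts number 0.70 × 116 = 81.2 under TAU and 0.875 × 116 = 101.5 under MAFT-D. So u = 2% means about 1.6 and 2.0 miscoded patients, and u = 5% about 4.1 and 5.1.

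**Unequal miscoding, same range.**

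- No true effect (30% in both arms), u = 5% under TAU and 2% under MAFT-D: 33.5% against 31.4%, a spurious difference of 2.1 points in favour of MAFT-D.
- Planned effect, u = 2% under TAU and 5% under MAFT-D: 31.4% against 16.9%. The odds ratio is (0.314 / 0.686) / (0.16875 / 0.83125) = 2.25.
- Planned effect, the reverse: 33.5% against 14.25%. The difference widens from 17.5 to 19.25 points.

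**The case against.** The strongest reply is that the sentence is merely compressed. Interviewing the therapist has no purpose for classification unless the answer counts, and the missing-data statement fits a sequence: ask the patient, then the therapist, and treat the case as missing only when both are gone. This is a plausible account of what was meant, and it disposes of a charge a reader might infer, that the two passages flatly contradict each other when patient and therapist have both left. The fallback presupposes a therapist to interview, so the missing-data statement can be read as the next step. What remains is that the endpoint section does not say that the therapist's report decides, and it should.

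A reader might also infer that patients who attend every week but ignore study contacts will be counted as dropouts in number. The documents do not support that. The interview has flexible timing, and therapists report therapy dropout as an event when it occurs, so the interview may be attempted only after a reported ending. The ongoing-therapy case is then rare or absent. The excluded-reason case remains.

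A third temptation is to use the 15% loss to follow-up as the value of u, which would take power down to about 66%. That figure concerns the BDI-II and describes therapists lost together with their patients. It is not a rate of unreachable non-dropouts whose therapist can still be interviewed.

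It also stands that equal miscoding is conservative for a superiority claim, that patients and interviewers are blinded, and that nothing in the documents shows contact rates to differ by arm. The planning rates come from reported dropout figures, which may already include some patients who could not be contacted. Finally, therapists know their allocation, so letting their account decide has a risk of its own.

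**Conclusion.** The point holds on the wording: consecutive sentences give incompatible codes to an unreachable patient whose therapy ended for an excluded reason, and to one still in treatment if the interview is also attempted then. It should be fixed because it concerns a primary endpoint, and staff or the author of the analysis plan could follow either sentence.

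The size cannot be derived from the documents. The fall in the odds ratio from 3.0 to about 2.75 to 2.5, and in power from 90% to about 87% to 83%, is an illustration. It assumes that 2% to 5% of true non-dropouts are miscoded, equally in both arms, and that 30% and 12.5% are free of such miscoding. Bias between the arms arises only if miscoding is unequal, which is possible but not shown. The documents do not support a claim that the trial is seriously underpowered or that the result will be biased.

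**What to change.** Replace the fallback sentence with a rule along these lines. If the patient cannot be reached, a blinded interviewer applies the same endpoint definition to the therapist interview, with session records where they exist.

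- Dropout: the therapist reports a premature end initiated by the patient, or therapy has stopped and the reason stays unknown.
- Not a dropout: therapy is ongoing, or it ended for an excluded reason.
- Missing: neither source is available. Align the missing-data statement under *Statistical analyses* with this.

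Record the source of every classification (patient, therapist, session records), state when the interview is attempted, and keep the coding of all unreachable patients as dropouts as a sensitivity analysis.

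The cost is a few sentences in the endpoint definition, a source field and a short derivation. The therapist interview is already planned. The drawback is that some classifications will rest on facts supplied by an unblinded therapist. Blinded judgement limits this, and the sensitivity analysis shows how far the result depends on it. Session records may be lacking for patients who leave the study but stay in therapy, so they can support the therapist interview but not replace it.
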